#### Secondary outcomes

For secondary outcomes, trends between baseline and follow-up time points (T0-T6) will be assessed using linear mixed models for repeated measures. This accounts for comfort of the cast, recovery of function and grip strength, pain severity (NRS), Q-DASH scores, PRWHE and EQ-5D-5L scores. The number of conversions to surgical fixation and complications will be determined using Fisher Exact or Chi-square test, depending on the magnitude of results.

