**Methods/design:**

This multicenter cluster randomized controlled trial will compare initial immobilization with a circumferential below-elbow cast versus a below-elbow plaster splint in reduced DRFs. Randomization will take place on hospital-level (cluster, *n* = 10) with a cross-over point halfway the inclusion of the needed number of patients per hospital. Inclusion criteria comprise adult patients (≥ 18 years) with a primary displaced DRF which is treated conservatively after closed reduction. Multiple trauma patients (Injury Severity Score ≥ 16), concomitant ulnar fractures (except styloid process fractures) and patients with concomitant injury on the ipsilateral arm or inability to complete study forms will be excluded. Primary study outcome is fracture redisplacement of the initial reduced DRF. Secondary outcomes are patient-reported outcomes assessed with the Disability Arm Shoulder Hand score (DASH) and Patient-Rated Wrist Evaluation score (PRWE), comfort of the cast, quality of life assessed with the EQ-5D-5L questionnaire, analgesics use, cost-effectiveness and (serious) adverse events occurence. In total, 560 patients will be included and followed for 1 year. The estimated time required for inclusion will be 18 months.

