### Objectives

The primary objective is to assess which type of cast, a splint versus a circumferential cast, is most optimal to prevent fracture redisplacement in adult patients with a reduced DRF.

As secondary objectives, we assess which type of casting results in fewer surgical interventions and complications. Thereby we will assess cost-effectiveness, the comfort of the cast, pain scores, functional outcome, patient-reported outcome and quality of life.

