### Design, participants, interventions and outcomes

#### Study design and randomization

For this study, a multicenter cluster randomized design is used. All participating hospitals are located in the Netherlands and include the following 10 centres; Alrijne hospital (Leiderdorp), Elisabeth-Tweesteden hospital (Tilburg), Erasmus MC University Medical Center (Rotterdam), Franciscus hospital, location Gasthuis and Vlietland (Rotterdam and Schiedam), Haga Teaching hospital (Den Haag), Haaglanden Medical Center (Den Haag), IJsselland hospital (Capelle aan den IJssel), Maasstad hospital (Rotterdam), Reinier de Graaf Gasthuis (Delft) and St. Antonius Hospital (Utrecht and Nieuwegein).

Two types of cast immobilization will be compared in this trial. Randomization at patient level will be challenging because of the 24/7 availability of the Emergency Department (ED), leading to a high number of treating physicians. To overcome the potential of many protocol violations, we chose to randomise on hospital-level with a cross-over point halfway the needed inclusions per hospital (i.e. after 31 inclusions). This means all patients in one hospital will receive the same intervention, which will change after half of the number of patients are included. This cross-over design is used to overcome potential non-eligibility of both groups because patient populations can differ amongst hospitals. Secondly, possible bias due to existing experience with one of the techniques in each hospital will be diminished. Before the start of the study, an independent researcher not involved in the study, randomly allocated the starting treatments amongst the participating hospitals.

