#### Sample size

The sample size calculation is based on the results of our recent retrospective study [14]. We hypothesize that fracture redisplacement occurs in 10% of circumferential casted patients versus 20% in splinted patients. A total of 500 patients is needed to detect superiority of a circumferential cast. The sample size calculation is based on a mixed-effects logistic regression, to account for clustering using a random intercept for the hospitals. The intra-class correlation coefficient between the different hospitals for the proportion of fracture redisplacement is assumed to be 0.06, which is generally reported in the literature for hospital processes. From the expected proportions of redisplacement in the two groups, we calculated the hospital-specific log odds of secondary displacement in the circular cast group, equal to − 2.275 and log odds ratio of redisplacement between the two groups equal to 0.84. This calculation is based on the formula that links the cluster-specific coefficients in the mixed-effects logistic regression with the population coefficients averaged over the hospitals. With a power of 93%, 50 patients per hospital need to be included, resulting in a total number needed of 500 (10 participating hospitals). Additionally, we also calculated the needed number of patients using a two-sample test for proportions. Using the same assumptions, namely difference between groups, a significance level of 0.05 and a power of 90%. This resulted in 490 needed patients in total. Accounting for a 10% loss to follow-up, a total of 560 (280 patients per group) are required.

To improve awareness of the study in all participating centers and thereby advert for reaching targeted sample size, a local investigator is appointed in each hospital. This local investigator is a physician who supervises the study. This person is easily accessible and will promote the study on a regular base. We send a newsletter every 2 months to inform about the study progression.

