#### Primary outcome

The primary outcome, fracture re-displacement, will be analyzed using a mixed-effects logistic regression. To account for clustering, a random intercept for the hospitals will be used. Fixed effects will be the covariates we adjust for as reported in the literature, namely age, presence of osteoporosis, and fracture characteristics. If new prognostic factors will be identified and reported in the literature, these factors will also be added as covariates.

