#### Cost-effectiveness analysis

Both cost-effectiveness (CEA) and cost-utility (CUA) analysis will be performed from a societal perspective. For the calculation of medical costs, we will use charges as published in Dutch guidelines as a proxy of real costs. The unit per price of the cast and splint application in patients with DRF will be calculated with the micro-costing method. Intramural costs (i.a. additional diagnostics, number of hospital visits, in case of hospital admission the length of stay etc.) are collected from the electronic health record. Productivity costs will be registered in detail by the iPCQ. The iMCQ and the iPCQ are validated by the Institute of Medical Technology Assessment (Erasmus University, Rotterdam, The Netherlands).

The difference in costs and effects of a circumferential cast instead of a splint will be calculated as incremental cost-effectiveness ratio (ICER). The primary effect outcome measures will be the number of re-displacements for the CEA and quality-adjusted life years (QALY) for the CUA. QALYs will be measured, based on the Dutch tariff for the EQ-5D-5L.

The sensitivity analysis will assess the robustness of the results to changes in costs and effect parameters. Bootstrapping with 5000 replications will be used to estimate 95% confidence intervals around cost differences and the uncertainty surrounding the ICERs. This will be graphically presented on cost-effectiveness planes and acceptability curves using the net benefit framework [28, 29]. For the time horizon of 1 year, discounting is not necessary.

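### Conversion to surgery and complications are tested as if patients were independent, although hospitals were randomised with a cross-over, so the nominal 5% error rate is not assured

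*Protocol article*

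**What the plan says.** The Objectives section lists first among the secondary aims that "we assess which type of casting results in fewer surgical interventions and complications". Under Data analysis, Secondary outcomes, the method for both is fixed: "The number of conversions to surgical fixation and complications will be determined using Fisher Exact or Chi-square test, depending on the magnitude of results". Neither test has a term for hospital or period.

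The design is given in the abstract: "Randomization will take place on hospital-level (cluster, *n* = 10) with a cross-over point halfway the inclusion of the needed number of patients per hospital". The section on study design and randomisation puts the switch after 31 inclusions. For the primary outcome the article says: "To account for clustering, a random intercept for the hospitals will be used". The sample-size section states: "The intra-class correlation coefficient between the different hospitals for the proportion of fracture redisplacement is assumed to be 0.06". It does not divide that correlation into a within-period and a between-period part, and it gives no ICC for surgery or complications.

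**The concern.** The unit allocated to a treatment is a hospital during one half of its recruitment. Fisher and chi-square tests take the patient as that unit. Within one trial, the primary outcome is thus analysed with clustering in mind and the next binary outcomes are not. A test is named, so this is a stated choice and not a detail left to a fuller document.

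The direction of the error depends on how hospitals vary over time. If a hospital's event rate is stable, each hospital contributes to both arms, its effect cancels, and the unstratified test is slightly conservative and loses some precision. If rates shift between the two halves of recruitment (staff, training, case mix), that shift is confounded with treatment inside the hospital, and an independent-patient test counts it as evidence. At stake are the p-values and intervals for surgery, which the Background presents as the thing to be avoided.

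**Working it through.** **Inputs from the article.** ICC 0.06; 10 hospitals; 560 patients; redisplacement 10% versus 20%.

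**Derived.** Patients per hospital-period m = 560 / (10 × 2) = 28.

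**Assumed.** Cluster autocorrelation (CAC, the ratio of between-period to within-period correlation), shown at 1, 0.9, 0.8 and 0.5. Event rates of 15% and 5%. The same ICC for surgery and complications as for redisplacement.

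**Step 1: on which scale is 0.06?** Reproduce the protocol's own log odds (−2.275) and log odds ratio (0.84). On the logit scale the hospital variance is 0.06/0.94 × π²/3 = 0.210. The usual approximation linking marginal to hospital-specific coefficients multiplies by √(1 + 0.346 × 0.210) = 1.0357.
- Log odds: ln(0.1/0.9) × 1.0357 = −2.197 × 1.0357 = −2.276.
- Log odds ratio: (−1.386 + 2.197) × 1.0357 = 0.811 × 1.0357 = 0.840.

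Exact numerical integration gives −2.28 and 0.83. So 0.06 was used on the logit scale.

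**Step 2: convert to the proportion scale.** Integrating the logistic-normal model with variance 0.210 gives a proportion-scale ICC of about 0.0266 at 15% events and 0.0106 at 5%.

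**Step 3: error rate of the independent-patient test.** The ratio of true to assumed variance is VR = 1 + (m − 1)ρ − mρ × CAC, and the type I error is 2 × [1 − Φ(1.96/√VR)]. For example, at 15% events and CAC 0.8, VR = 1 + 27 × 0.0266 − 28 × 0.0266 × 0.8 = 1.122, giving 6.4%.

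| CAC | VR, 15% events | Type I error | VR, 5% events | Type I error |
|---|---|---|---|---|
| 1 | 0.973 | 4.7% | 0.989 | 4.9% |
| 0.9 | 1.048 | 5.6% | 1.019 | 5.2% |
| 0.8 | 1.122 | 6.4% | 1.049 | 5.6% |
| 0.5 | 1.345 | 9.1% | 1.138 | 6.6% |

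**Step 4: sensitivity to the scale.** If 0.06 is instead read directly as a proportion-scale ICC, VR is 0.94, 1.108, 1.276 and 1.78, and the type I error is 4.3%, 6.3%, 8.3% and 14.2%. Step 1 speaks against that reading, so these are upper figures.

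**Step 5: simulation with logit-scale ICC 0.06 and m = 28.**

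| Events | CAC | Chi-square | Fisher | Paired hospital-level t test |
|---|---|---|---|---|
| 15% | 1 | 4.8% | 3.7% | 5.0% |
| 15% | 0.8 | 6.5% | 5.2% | 5.0% |
| 15% | 0.5 | 8.8% | 6.8% | 4.5% |
| 5% | 1 | 5.0% | 3.1% | 4.6% |
| 5% | 0.8 | 5.4% | 3.5% | 4.5% |
| 5% | 0.5 | 6.8% | 4.4% | 4.8% |

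The simulation agrees with Step 3. The hospital-level comparison stays at or just under 5% throughout.

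**The case against.** The strongest reply is that the cross-over already protects the simple test. The protocol assumes a hospital effect only, every hospital supplies both arms, and under that assumption the test is near nominal or slightly conservative. This stands. Inflation needs hospital-by-period variation, for which the article gives no value. It also stands that Fisher remains below 5% in the rare-event settings simulated, which is where it would be used.

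Nor is the primary model a complete benchmark. With only a hospital intercept it too omits hospital-by-period variation, so copying it to surgery would not remove the source of inflation.

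Three stronger readings are tempting and are not supported:
- **That the economic intervals ignore clustering.** The article says "Bootstrapping with 5000 replications will be used to estimate 95% confidence intervals around cost differences and the uncertainty surrounding the ICERs", but not whether patients, hospitals or hospital-periods are resampled. A condensed article may leave that to the full plan.
- **That the linear mixed models for repeated measures omit hospital.** Their random-effects structure is not given, so nothing shows that hospital is excluded.
- **That surgery clusters at least as strongly as redisplacement.** No figure in the article supports this, and a stable hospital habit would be balanced by the cross-over.

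What the reply does not remove is the mismatch itself. If periods do not differ, the named tests give up some precision. If periods differ, chi-square exceeds its nominal level.

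**Conclusion.** The point holds for the Fisher and chi-square sentence, as a mismatch between design and analysis whose consequence is conditional. A reader might infer that the error rates for these outcomes are simply wrong; the protocol's own assumptions do not show that. Under a hospital-only effect the chi-square error is about 4.7% at 15% events. It rises to about 5.6%, 6.4% and 9.1% at CAC 0.9, 0.8 and 0.5, and lies between about 5% and 7% at 5% events. These figures rest on a logit-scale ICC of 0.06 carried over from redisplacement, balanced periods of 28, and assumed CAC values and event rates. The outcomes are secondary, so this should be corrected before analysis but does not threaten the primary result.

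**What to change.** **Conversion to surgery.** Replace the Fisher or chi-square test with a mixed-effects logistic regression that has treatment and period as fixed effects and hospital and hospital-by-period as random effects. A paired hospital-level comparison of the two halves is an alternative.

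**Sparse complications.** Use an exact test stratified by hospital, or a permutation test over the hospitals' starting order. The permutation test follows the actual randomisation and is the safer choice if periods may differ. Stratifying by hospital does not by itself absorb hospital-by-period variation: a simulated hospital-stratified Mantel-Haenszel test rejected 6.7% and 9.1% of the time at CAC 0.8 and 0.5 with 15% events. If five hospitals start with each treatment (an assumption), there are 10!/(5! × 5!) = 252 arrangements, so the smallest two-sided p-value is about 2/252 = 0.008, which is fine enough for a 5% test.

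**Cost.** A change of wording and a little programming, with no change to trial conduct. Intervals may widen, and the paired hospital-level test costs power because it has only ten pairs. With the primary outcome's 10% versus 20%, 25 patients per hospital-period and CAC 1, simulated power was about 81%, against about 90% for a hospital-stratified test. That favours the mixed model for surgery where there are enough events to fit it.

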#### Cost-effectiveness analysis

Both cost-effectiveness (CEA) and cost-utility (CUA) analysis will be performed from a societal perspective. For the calculation of medical costs, we will use charges as published in Dutch guidelines as a proxy of real costs. The unit per price of the cast and splint application in patients with DRF will be calculated with the micro-costing method. Intramural costs (i.a. additional diagnostics, number of hospital visits, in case of hospital admission the length of stay etc.) are collected from the electronic health record. Productivity costs will be registered in detail by the iPCQ. The iMCQ and the iPCQ are validated by the Institute of Medical Technology Assessment (Erasmus University, Rotterdam, The Netherlands).

The difference in costs and effects of a circumferential cast instead of a splint will be calculated as incremental cost-effectiveness ratio (ICER). The primary effect outcome measures will be the number of re-displacements for the CEA and quality-adjusted life years (QALY) for the CUA. QALYs will be measured, based on the Dutch tariff for the EQ-5D-5L.

The sensitivity analysis will assess the robustness of the results to changes in costs and effect parameters. Bootstrapping with 5000 replications will be used to estimate 95% confidence intervals around cost differences and the uncertainty surrounding the ICERs. This will be graphically presented on cost-effectiveness planes and acceptability curves using the net benefit framework [28, 29]. For the time horizon of 1 year, discounting is not necessary.

### Data management

All data are handled confidentially and anonymized in compliance with the Dutch Personal Data Protection Act. Personal data of participants will be changed by a study number. This number is used for all study documentation, study reports and publications. The key of this study number will be handled by an independent researcher. During the study period, all data will be collected and managed using GemsTracker electronic data capture tools hosted at Erasmus Medical Center [19]. Paper case report forms are entered in GemsTracker by the researcher and the original paper case forms will be filed in the investigator site file at the recruiting hospital. All data is stored for 15 years.

#### Data monitoring

Since the study is labelled as low risk, a data safety monitoring board is not required. However, the study will be monitored at least once a year by an independent monitoring board. A written report will be available from all monitors.

The investigator will submit a progress report to the accredited Medical Research Ethics Committee of Erasmus Medical Center in Rotterdam throughout the clinical trial annually. This will consist of the date of inclusion of the first subject, numbers of subjects included and numbers of subjects that have completed the trial, SAEs, other problems and amendments.

#### Dissemination

We plan to present the study results at (inter) national conferences and submit the manuscript to general peer-review journals. We aim to implement the study results in the Dutch guideline for DRFs.

## Discussion

This study is an open-label trial. Allocated treatments are visually different for the treating physician and the patient. Randomization status will therefore not be blinded.

Heterogeneity of the study population concerning fracture characteristics and age could be pointed out as a limitation. However, this pragmatic study tries to represent the actual patient population.

## Data Availability

The datasets used and/or analyzed during the current study are available from the corresponding author on reasonable request.

## Abbreviations

DRF: Distal radius fracture
ED: Emergency Department
PIF: Patient Information Folder
ISS: Injury Severity Score
PA: Posterior-anterior
PACS: Picture Archiving and Communication System
ICC: Intraclass Correlation Coefficient
NRS: Numeric Rating Scale
Q-DASH: Quick Disabilities of the Arm, Shoulder and Hand
PRWHE: Patients-Rated Wrist Hand Evaluation
EQ-5D-5L: 5-level EuroQol
iMCQ: Medical Consumption Questionnaire
iPCQ: Production Consumption Questionnaire
ROM: Range of motion
DRUJ: Distal radioulnar joint
SAE: Serious adverse event
CCMO: Central Committee on Research Involving Human Research
CRPS: Complex regional pain syndrome
CEA: Cost-effectiveness analysis CUA Cost-utility analysis
ICER: Incremental cost-effectiveness ratio
QALY: Quality-adjusted life year
